#### Main efficacy study **(Changes have been made to analysis plan – please refer to appendix for the updated analysis plan)**

##### Primary outcome analyses of 12-month RFS

- ~~The primary analysis for RFS efficacy will be a multivariable logistical regression analysis with 12-month RFS as endpoint including the following 7 parameters: treatment arm, age, PCI, use of systemic perioperative chemotherapy (neoadjuvant and/or adjuvant), liver metastases resection, colon or rectal primary, and lymph-node metastasized primary tumor.~~
- ~~A Fisher’s exact test for 12-month RFS between the arms~~

~~Secondary outcome analyses of total RFS~~

- ~~A Kaplan-Meier curve with two-tailed log rank test between the arms with RFS up to 5 years as endpoint (i.e. time to recurrence)~~
- ~~A multivariable Cox regression analysis with RFS (i.e. time to recurrence) as endpoint including the following 7 parameters: Treatment arm, age, PCI, use of systemic perioperative chemotherapy (neoadjuvant and/or adjuvant), liver metastases resection, colon or rectal primary, and lymph-node metastasized primary tumor.~~
- The same analyses above may be run against peritoneal recurrence-free survival.

If any of the analyses above show a significant result, the trial will conclude that the intensified HIPEC arm indeed improves the locoregional effect of HIPEC compared to the current standard HIPEC.

If the interim analysis results demonstrate that overall survival is attainable as primary endpoint, a new statistical analysis will be set up after a renewed sample size calculation.

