## Justification of administration route

The concept of both HIPEC and early postoperative intraperitoneal chemotherapy (EPIC) is to maximize the effect of chemotherapy on the peritoneum in order to prevent locoregional recurrence. The surgical treatment (cytoreductive surgery) is aimed at removing all visible tumor tissue from the peritoneum. The aim of the perioperative chemotherapy treatments of HIPEC and EPIC is then to eradicate potentially remaining microscopic peritoneal disease. It is well-known that the chemotherapy distribution from the bloodstream to the peritoneal cavity is limited due to the blood-peritoneal barrier. Therefore, this trial is using two intraperitoneal chemotherapy treatment options instead of systemic chemotherapy.

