## Justification of Study design

The reason for going from a phase I to III combined approach is that the triple drug treatment (oxaliplatin, irinotecan, and 5-FU) has already been used in the medical oncology clinic as a routine clinical treatment for many years with a well-known and reported toxicity profile; and it has also, in some countries, been used in the HIPEC setting with 5-days of 5-FU EPIC. The initial plan was to do a direct phase III study. However, since it is planned to give a single dose of 5-FU instead of 5 daily treatments, it will probably be possible to increase the concentration of 5-FU EPIC. As such, the study committee opted to do a dose-titration study (phase I) including 15-30 patients to evaluate the possibility of using a slightly higher single dose 24-hour 5-FU. Instead of a phase II trial, an interim analysis after treatment of the first 140 patients in phase III was added to evaluate safety and aim for a phase III final comparison including 326 patients.

The rationale behind two investigational drugs (irinotecan and 5-FU) is that adding only one drug is not enough to provide a synergy that can produce a reasonable investigational clinical effect (see figure 1). The dose-titration of irinotecan to oxaliplatin HIPEC has already been performed [14]. Thus, the phase I part of the trial is investigating the addition of 5-FU EPIC in a dose-titration manner to oxaliplatin + irinotecan HIPEC. The phase III part of the trial requires both drugs to be added for efficacy reasons and it is not feasible clinically to have several trial arms. Since the triple drug combination has already been in use in France with cytoreductive surgery and the combination is well studied and in use in clinical routine medical oncology treatment for metastasized colorectal cancer, it is the synergy of all three drugs combined with cytoreductive surgery that is being studied in phase III. Hence, all conclusions will be related to the combination treatment as such.

The risks of adding 5-FU EPIC to HIPEC has been reviewed already in several trials [7]. The risk of morbidity, reoperation, or postop mortality is not increased [6]. Although, one particular side-effect of neutropenia is expected to increase, it does not increase the risk of other morbidity [8]. In order to offset this side-effect, a planned bone marrow stimulation treatment will be administered.

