### Phase III

- Recurrence-free survival at 12 months.

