# ASSESSMENT OF EFFICACY

The primary endpoint in the efficacy trial is RFS after 12 months. Data from the one-year postoperative clinical follow-up that is registered in the HIPEC registry will be retrieved. Besides the site of relapse, also the date of recurrence is retrieved. It is defined as the date of the radiological examination that identifies the recurrence. Crude overall survival will also be assessed at the end of the trial follow-up as a secondary endpoint for the trial. The HIPEC registry is automatically connected with the Swedish death registry and therefore the overall survival follow-up is completely automatic as to the date of death. However, cause of death will also be retrieved from the cause of death registry in order to perform exploratory analyses of cancer specific survival. Likewise, quality-of-life will be retrieved from the HIPEC registry as well.

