## Clinical and laboratory assessments

### Timing and method of the assessment

The dose titration is assessed continuously as each dose level is completed. All morbidity data is retrieved from the HIPEC registry.

Patient follow-up:

Mandatory

- Abdominal and thoracic CT scan at baseline before surgery and 12 months postoperatively.
- Treatment administered (CRS+HIPEC+EPIC variables)
- Morbidity to be submitted within 30 days from treatment administration. SAE and SUSAR are to be reported immediately (a separate section will make this possible in the HIPEC registry)
- Overall survival follow-up at
- 5 years from the HIPEC registry

Clinical routine

- The following follow-up is standard in Sweden after CRS+HIPEC: CT scan and tumor markers every 6 months for 2 years and then annually for another 3 years. Since all these follow-ups are not included in the HIPEC registry, we will not include them in the schedule of investigational events.
- EORTC QLQ-C30, CR29, and STO22 questionnaires filled out at baseline, 3, 12 and 36 months after surgery using the established QoL database. All patients are included in the quality-of-life registry as part of the clinical quality assurance follow-up, unless they specifically have requested not to be included.

Optional: Sending intraoperative tumor tissue to Uppsala for chemoresistance testing within 48 hours. Tissue is discarded right after testing. No biobanking will occur.

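### The protocol's unstruck conclusion rule reads a significant any-site RFS result as an improved locoregional effect, which only the optional peritoneal RFS analysis could show

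*Protocol*

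**What the plan says.** The phase III primary endpoint (section 7.1.2) is "Recurrence-free survival at 12 months", with no restriction by site. Section 11 records where the relapse occurred as an additional item: "Besides the site of relapse, also the date of recurrence is retrieved". The mandatory imaging in section 11.1.1 covers the chest as well as the abdomen: "Abdominal and thoracic CT scan at baseline before surgery and 12 months postoperatively". Patients with up to three liver metastases are eligible (section 9.1).

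In section 13.2.1, under the main efficacy study, the bullets for 12-month RFS and for total RFS are struck through, and the heading refers to an appendix for the updated plan. Two items there are not struck. One is the peritoneal bullet: "The same analyses above may be run against peritoneal recurrence-free survival". The other is the conclusion rule, triggered by significance in any one of the listed analyses: "the trial will conclude that the intensified HIPEC arm indeed improves the locoregional effect of HIPEC compared to the current standard HIPEC".

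On scope, section 5.4 says that "all conclusions will be related to the combination treatment as such". Section 5.3 gives the purpose of both HIPEC and EPIC, which "is to maximize the effect of chemotherapy on the peritoneum in order to prevent locoregional recurrence".

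**The concern.** The rule fixes in advance what a positive trial will be said to have shown. By section 5.3, a locoregional effect is an effect on peritoneal recurrence. RFS is wider: a liver or thoracic recurrence ends recurrence-free status just as a peritoneal one does. A significant difference in RFS shows that fewer patients failed, not where the failures were prevented.

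The analysis that looks at the right sites need not be run under section 13.2.1, and peritoneal RFS is not among the secondary endpoints in section 7.2. As written, the trial could state a site-specific conclusion without a site-specific analysis. This is separate from how many tests feed the rule: one perfectly controlled RFS test would leave the same gap.

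There is also a smaller wording conflict. The rule credits the effect of HIPEC, while section 5.4 ties every conclusion to the combination.

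**Working it through.** **1. The passages side by side**

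| Place in protocol | What it fixes |
|---|---|
| 7.1.2 | Primary endpoint is 12-month RFS, any site |
| 11 and 11.1.1 | Site is retrieved; CT covers abdomen and thorax |
| 5.2 | Peritoneal RFS is named as a particular part of the RFS benefit |
| 13.5 | RFS, peritoneal RFS and pattern of recurrence are listed as separate outcomes |
| 13.2.1 | Any significant analysis gives a locoregional conclusion; peritoneal RFS is optional |

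The protocol itself separates RFS from peritoneal RFS, so the step from the first to a locoregional conclusion is not supplied by its definitions.

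**2. The plan's own sample size**

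Inputs (section 13.3): 12-month RFS 50% vs 66%, alpha 5% (taken as two-sided), power 80%.

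- Arcsine formula: h = 2·asin(√0.66) − 2·asin(√0.50) = 0.3257; n = 2(1.960 + 0.842)²/h² = 148 per arm.
- The pooled-variance formula gives 149.
- 148 × 1.10 = 162.8, so 163 per arm and 326 in total.

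The stated figures reproduce. They are powered on any-site RFS; there is no calculation for a peritoneal endpoint.

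**3. Smallest significant RFS result at 148 per arm, control at 50% (74/148)**

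- Pooled z-test at 61.4%: p̄ = 0.557; z = 0.114/√(2 × 0.557 × 0.443/148) = 1.97.
- Fisher's exact test (the unadjusted test in the struck text): 91/148 (61.5%) gives p = 0.061; 92/148 (62.2%) gives p = 0.046.

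**4. Can that result arise with no peritoneal effect?**

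Assume constant hazards. Let s be the share of the control-arm failure hazard that is not peritoneal recurrence. The documents do not give s, so a range is shown. With no effect on peritoneal recurrence, the hazard ratio needed on the rest is

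HR = 1 − (H_A − H_B)/(s·H_A), where H = −ln(12-month RFS).

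H_A = −ln 0.50 = 0.693. H_B = −ln 0.614 = 0.488 (z-test) or −ln 0.6216 = 0.475 (Fisher).

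| s (assumed) | HR needed, z-test | HR needed, Fisher |
|---|---|---|
| 30% | 0.01 | none (formula gives −0.05) |
| 50% | 0.41 | 0.37 |
| 70% | 0.58 | 0.55 |

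Example, z-test at s = 50%: 1 − (0.693 − 0.488)/(0.5 × 0.693) = 0.41.

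**5. The same at the full planned benefit**

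A simulation used 148 per arm, exponential times, no peritoneal effect, and the whole move from 50% to 66% placed on extraperitoneal recurrence. With assumed extraperitoneal shares of 50% to 70%, the extraperitoneal hazard ratio is 0.20 to 0.43. Fisher's test on any-site 12-month RFS was significant in about 76% of simulated trials, and a log-rank test of peritoneal recurrence in about 5%, the nominal level. This is an extreme construction. It shows that the two questions can have different answers, not that they will.

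**The case against.** The strongest reply is that the section is marked as changed. Every any-site RFS bullet above the sentence is struck, and the only live bullet is peritoneal RFS, for which a locoregional conclusion is fair. The sentence may be a leftover that the appendix already replaces. This stands as a limit on the point. However, the sentence is not struck, it sits under the 12-month RFS heading, and the peritoneal bullet defines itself by reference to the struck analyses.

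A reader might infer that the comparison itself is invalid because arm B adds EPIC, irinotecan, a different oxaliplatin dose and prophylactic G-CSF. The documents do not support that. The intensified arm is the protocol's label for the regimen including EPIC (sections 8.2.2, 16.2 and 16.3), EPIC is itself aimed at the peritoneum (section 5.3), and section 5.4 ties conclusions to the combination. Only the wording conflict remains.

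A reader might also infer that peritoneal outcomes will be ignored, or that an RFS gain would probably come from elsewhere. Section 13.5 names peritoneal RFS and pattern of recurrence among the differences considered for futility, and section 11 retrieves the site. Section 5.2 expects the benefit to be mainly peritoneal. The protocol's remarks on neutropenia as a favourable factor (sections 10.1 and 16.2) do not mention site of recurrence, so they do not establish an extraperitoneal benefit.

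Finally, the site shares are assumed, and zero peritoneal effect from an intraperitoneal regimen is an extreme case. That is correct; the figures are illustrative only.

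**Conclusion.** The point holds in a limited form. While the sentence remains in force, it lets a significant any-site RFS result be reported as a locoregional effect, which does not follow from that endpoint. A significant peritoneal RFS analysis could support the wording, but that analysis is optional. The reference to an effect of HIPEC is looser than section 5.4 and should be brought into line with it; the randomised contrast is sound for the combined regimen.

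The size cannot be fixed from the documents, because it depends on the site mix. Under constant hazards and no peritoneal effect, the gap is a real possibility if half or more of the failure hazard is extraperitoneal, though it then needs a strong extraperitoneal effect, and it essentially disappears at 30%. Whether the sentence still governs depends on the appendix. The point affects what the trial may conclude, not its sample size or its primary test.

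**What to change.** If the appendix supersedes the sentence, strike it along with the analyses already struck.

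Otherwise:

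- Replace it with: *A significant primary result will be concluded as improved 12-month RFS with the combined regimen (oxaliplatin/irinotecan HIPEC plus 5-FU EPIC) versus oxaliplatin HIPEC.* This also removes the conflict with section 5.4.
- In the peritoneal RFS bullet, change the optional wording to a commitment (*will be run*), using the site of relapse already retrieved under section 11.
- Allow locoregional wording only from that peritoneal analysis.

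The cost is a narrower headline claim, a wording amendment and one more analysis. No new data collection is needed.

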##### Secondary outcome analyses of overall survival and QoL:

- Overall survival up to 5 years will be compared with Kaplan-Meier and log-rank test as well as multivariable Cox regression using the following same variables as RFS: Treatment arm, age, PCI, use of systemic perioperative chemotherapy (neoadjuvant and/or adjuvant), liver metastases resection, colon or rectal primary, and lymph-node metastasized primary tumor.
- Quality of life between the two arms will be compared. The primary outcome is the comparison of questions 29 and 30 from the QLQ-C30 at 12 months and 36 months. The primary statistic will be a Mann-Whitney U test of difference for both question 29 and 30 between the arms. The secondary statistic will be a comparison of mean differences for question 29 and 30 between baseline and 12-months using a Freidman’s repeated measures ANOVA test. Specifically, differences between the sexes will be investigated.
- Three specific subgroup multivariable analyses using RFS as endpoint will be performed using the same variables as above for correction: (1) PCI score – the score will be grouped 1-10, 11+, (2) Signet cell cancer, (3) previously given oxaliplatin-based therapy, (4) +/- livermetastases.
- Further exploratory and post hoc analysis of subgroups will be performed: multivariable analysis for overall survival and forest plots.

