| Criteria for evaluation:  Safety: Safety will be assessed by the Clavien-Dindo classification and reporting of Adverse Events.  The maximum tolerated dose of 5-FU will be determined by giving the first 15-30 patients escalating doses of 5-FU. The morbidity of each dose level of 5-FU 24-hour EPIC will be evaluated by the Data Monitoring Committee 30 days post-treatment. A dose level with ≤1/3 or ≤2/6 with 3b-4 Clavien-Dindo morbidity may proceed to the next dose level. Following the dose titration study, all patients will receive the maximum dose of 5-FU. An interim safety evaluation will be performed after the first 140 patients have been randomized and treated with HIPEC or HIPEC in combination with EPIC. The Clavien-Dindo grade 3-5 morbidity is expected to be approximately 0.35 (35%). If the experimental arm’s 95% CI falls within 0.4 or below, the study will be allowed to continue.  Efficacy: Recurrence free survival (RFS) is determined at 12-months post treatment through the HIPEC registry. Postoperative complications rates with-in 30 days, 5-year overall survival and RFS are further determined through the HIPEC registry and quality of life is assessed by questionnaires through the QoL registry. | | |
| **Dosage of Investigational Products:**  The maximum tolerated dose (MTD) of 5-FU will be determined by giving the first 15-30 patients escalating doses of 5-FU. The morbidity of each dose level of 5-FU 24-hour EPIC will be evaluated by the Data Monitoring Committee within 30 days post-treatment. A dose level with ≤1 of 3 patients or ≤2of 6 patients (extended group size) with 3b-5 morbidity may proceed to the next dose level. If the frequency of 3b-5 morbidity is higher, MTD has been passed and the dose of 5-FU in the efficacy study will be the next lower dose level. If MTD is not reached the highest dose level of 5-FU (850 mg/m^2^) will be used. | | |
| Statistical methods:  Recurrence free and overall survival of the two arms will be compared using the parameters: treatment arm, age, PCI, CC score, use of systemic perioperative chemotherapy (neoadjuvant and/or adjuvant), concomitant liver metastases resection, colon or rectal primary tumor, and lymph-node metastasized primary tumor.  QoL will be analyzed by comparing the answers to questions 29 and 30 in QLQ-C30 by Mann-Whitney U test and Freidman’s repeated measures ANOVA test. Specifically, differences between the sexes will be investigated.  Statistical significance will be set at p=0.05. | | |

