## Schedule of events

Table 3. Schedule of investigational events.

|  | Preop Visit | Day of treat-ment | 1  In-hospital | 2  In-hospital | 3  Out-patient | 4  Out-patient | 5  Out- patient | 6  Out-patient | 7  EOS |
| --- | --- | --- | --- | --- | --- | --- | --- | --- | --- |
|  | -1m | 0 d | 5 d ± 2 | 10 d ± 3 | 30 d +2m | 90 d  ±4m | 1y ±3m | 3 y ±3m | 5 y ±3m |
| Physical examination  (eCRF follow-up) | x |  | x | x |  |  |  |  |  |
| Telephone follow-up  (eCRF follow-up) |  |  |  |  | x | x | x | x |  |
| eCRF Inclusion/screening | x |  |  |  |  |  |  |  |  |
| Signed informed consent | x |  |  |  |  |  |  |  |  |
| Randomization* |  | x* |  |  |  |  |  |  |  |
| CRS + HIPEC/EPIC treatment data  HIPEC registry treatment section |  |  |  |  |  | x |  |  |  |
| eCRF Drugs – medication/chemotherapy** | x |  |  |  |  | x |  |  |  |
| CT scan |  |  |  |  |  |  | x |  |  |
| eCRF Blood work*** |  |  |  |  | x |  |  |  |  |
| Questionnaire (QLQ-C30, CR29, STO22) HIPEC registry acquired | x |  |  |  |  | x | x | x |  |
| Morbidity from HIPEC registry (incl. eCRF AER/eCRF follow-up) |  |  | x | x | x |  |  |  |  |
| Overall survival HIPEC registry§ |  |  |  |  |  |  |  |  | x |
| Recurrence free survival HIPEC registry |  |  |  |  |  |  | x | x | x |

* only after the maximum tolerated dose of 5-FU has been determined

** (-1m) – previous chemotherapy and current medications, (90d) adjuvant chemotherapy administered

*** CEA, CA 19-9, CA 125 are taken preoperatively (-1m). Haemoglobin, C-reactive protein (CRP), white blood cell count (WBC), neutrophil count, platelet count, albumin, creatinine, alanine transaminase (ALT) are taken preoperatively and postoperatively 5 times during the first 10 days. The lowest haemoglobin, highest CRP, lowest neutrophil and WBC, lowest platelet count, lowest albumin, highest creatinine, highest ALT will be registered in the eCRF blood work.

§ Overall survival from HIPEC registry is also acquired prior to interim analysis

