## RandomiZation and blinding

Patient randomization will be integrated into the HIPEC registry and will be performed intraoperatively after abdominal exploration and after a CC 0 result is deemed achievable. For patients with isolated peritoneal metastases, there will be center stratification and PCI stratification (PCI 1-10 vs 11+). For patients with combined liver and peritoneal metastases, there will be only PCI stratification (PCI 1-10 vs 11+). Multivariable regression will be used in the results section in order to account for skewed differences in baseline differences. See the planned statistical analyses (13.2).

There is no blinding involved in this trial. This is mainly due to the fact that one arm will need to receive G-CSF treatment postoperatively; and thus, the treating physician needs to know which arm the patient is allocated to. The primary endpoint is recurrence free survival which is determined by radiologists on a CT scan. The radiologists will not be privy to the treatment allocation. Thus, there is a blinding of primary endpoint evaluation.

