#### Health-related quality-of-life assessment

EORTC QLQ-C30 and CR29 and STO22 forms will be used to evaluate quality-of-life [10]. These forms will be sent out at baseline, 3, 12, and 36 months. The primary outcome is the comparison of questions 29 and 30 from the QLQ-C30 at 12 months rated 1-7, where 1 is very poor and 7 is excellent.

QLQ-C30 questions for QoL assessment:

29. How would you rate your overall health during the past week?

30. How would you rate your overall quality of life during the past week?

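### The primary QoL statistic is an unadjusted Mann-Whitney test, although each patient's answer to the same question is collected before randomisation; it is valid but less efficient than a baseline-adjusted comparison

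*Protocol*

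**What the plan says.** Section 13.2.1, under the secondary analyses of overall survival and QoL, sets the outcome: "The primary outcome is the comparison of questions 29 and 30 from the QLQ-C30 at 12 months and 36 months". It then names the test: "The primary statistic will be a Mann-Whitney U test of difference for both question 29 and 30 between the arms". Baseline appears only in the next sentence: "The secondary statistic will be a comparison of mean differences for question 29 and 30 between baseline and 12-months using a Freidman’s repeated measures ANOVA". The QoL bullet is not struck through.

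The synopsis (Statistical methods) gives the same between-arm test, "QoL will be analyzed by comparing the answers to questions 29 and 30 in QLQ-C30 by Mann-Whitney U test", and adds the Friedman test without ranking the two.

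On data collection, section 11.1.1 says "These forms will be sent out at baseline, 3, 12, and 36 months". The row "Questionnaire (QLQ-C30, CR29, STO22) HIPEC registry acquired" in Table 3 (section 8.3) places the first questionnaire at the preoperative visit. Section 10.5 says "Patient randomization will be integrated into the HIPEC registry and will be performed intraoperatively". The baseline answer is therefore obtained before randomisation.

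Section 11.1.1 words the outcome as "The primary outcome is the comparison of questions 29 and 30 from the QLQ-C30 at 12 months rated 1-7" and does not mention 36 months. The two sections differ on the time points.

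**The concern.** A value measured before randomisation on the same item is usually among the strongest predictors of the follow-up answer, and treatment cannot have affected it. A comparison that leaves it out carries between-patient variation that could be removed at no cost in data. The secondary Friedman test does not fill the gap: it compares time points within patients and does not estimate a difference between arms adjusted for baseline.

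Section 16.2 brings in quality of life to follow the patient's view of side effects against benefit. A less precise comparison is more likely to miss a real difference in either direction. The number of QoL answers at 12 and 36 months will also fall below the number randomised, through deaths, withdrawals and non-response.

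**Working it through.** **No QoL figure to reproduce.** The protocol gives no QoL sample size, effect size, SD, correlation or power. The patient numbers are taken from the RFS calculation in section 13.3, which reproduces. For 50% against 66%, two-sided 5% and 80% power, the arcsine formula gives h = 2·asin(√0.66) − 2·asin(√0.50) = 0.3257 and n = 2·((1.960 + 0.842)/0.3257)² = 148 per arm. The pooled normal formula gives 149. Then 148 × 1.1 = 162.8, or 163 randomised per arm, and 163 × 0.9 = 146.7, or 147 after 10% loss.

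**Assumptions.** n of 147 to 163 per arm; effect δ of 0.30 to 0.40 SD; baseline-to-follow-up correlation ρ of 0.3, 0.5 or 0.7; two-sided 5%.

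**Formula.** Let k = δ·√(n/2).
- Unadjusted power ≈ Φ(k − 1.96).
- Baseline-adjusted power ≈ Φ(k/√(1 − ρ²) − 1.96), because adjustment leaves a residual variance of 1 − ρ². At ρ = 0.5 that is 0.75, a 25% cut.

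Example: n = 163, δ = 0.30, ρ = 0.5. k = 0.30 × √81.5 = 2.708. Unadjusted: Φ(0.748) = 77.3%. Adjusted: Φ(2.708/0.866 − 1.96) = Φ(1.167) = 87.8%. The gain is 10.6 points before rounding.

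| n per arm | δ (SD) | Unadjusted power | Gain, ρ 0.3 | Gain, ρ 0.5 | Gain, ρ 0.7 |
|---|---|---|---|---|---|
| 147 | 0.30 | 73.0% | 3.9 | 11.4 | 22.0 |
| 147 | 0.40 | 92.9% | 2.0 | 4.8 | 6.9 |
| 163 | 0.30 | 77.3% | 3.7 | 10.6 | 19.4 |
| 163 | 0.40 | 95.1% | 1.5 | 3.6 | 4.8 |

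**Simulation of a 7-category item.** Mann-Whitney against rank analysis of covariance, 2,000 runs per setting, gain in power points:

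| n per arm | δ (SD) | ρ 0.3 | ρ 0.5 | ρ 0.7 |
|---|---|---|---|---|
| 148 | 0.30 | 4.0 | 9.9 (68.9% to 78.8%) | 22.0 |
| 148 | 0.40 | 1.6 | 5.1 (90.4% to 95.5%) | 8.1 |
| 163 | 0.30 | 3.4 | 10.1 (73.2% to 83.3%) | 18.7 |
| 163 | 0.40 | 1.7 | 4.1 (93.4% to 97.5%) | 6.9 |

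A separate simulation with 147 per arm and 0.34 SD gave 79% to 82%, 78% to 87% and 80% to 95% at ρ of 0.3, 0.5 and 0.7, with a false-positive rate of about 5%. Formula and simulation agree on about 2 to 4, 4 to 11 and 5 to 22 points.

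**If the test is meant on change scores.** The variance of a change score is 2(1 − ρ). The adjusted variance divided by this is (1 − ρ²)/(2(1 − ρ)) = (1 + ρ)/2, that is 0.65, 0.75 and 0.85 at the three correlations, so the adjusted comparison is the more precise each time. Simulated power (147 per arm, 0.34 SD) for change scores against the adjusted test was 65% against 82%, 78% against 88% and 92% against 96%.

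**The case against.** The strongest reply is that nothing here is wrong in the strict sense. Under randomisation the unadjusted Mann-Whitney test keeps its error rate, and a rank test suits an item scored 1 to 7. A reader might infer that the planned QoL comparison is biased or invalid. The documents do not support that: chance baseline imbalance adds noise, not systematic error.

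A reader might also want a single figure for the lost power. The protocol does not fix one. The result depends on an effect size, SD, correlation and number of QoL responders that it does not give, and across 0.2 to 0.5 SD at 163 per arm and ρ = 0.5 the formula gain runs from 0.5 to 12.4 points. That objection stands, so only a range is given. Nor does the precision gain change the trial's size, which RFS determines.

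Three textual points also bear on this.
- Section 10.5 promises multivariable regression for baseline differences. The sentence is general, and section 13.2.1 does not carry it into the QoL analysis.
- The heading of the main efficacy section points to an updated analysis plan in an appendix that is not shown. The QoL bullet is not struck through, unlike most of the RFS bullets, so it reads as current, but the updated plan may differ.
- The wording of the test could mean change from baseline. Baseline would then be used, but less efficiently than by adjustment.

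Covariate choices for a secondary endpoint are often left to the SAP. Here, however, the protocol itself names the test and ranks it as primary for QoL.

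**Conclusion.** The point holds as a matter of efficiency. The protocol fixes an unadjusted arm comparison as the primary QoL statistic while collecting a pre-randomisation answer to the same question, and no other stated analysis gives a baseline-adjusted comparison of the arms. On the assumptions above, the planned test gives up about 2 to 4 power points at ρ = 0.3, 4 to 11 at ρ = 0.5 and 5 to 22 at ρ = 0.7, with the low ends where power is already above 90%. The correlation at 36 months may differ from that at 12 months, and neither is stated. Low priority: a secondary endpoint, a valid test and an inexpensive improvement.

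**What to change.** In section 13.2.1 and the matching synopsis line, make the primary QoL statistic a baseline-adjusted comparison of the arms, separately for questions 29 and 30, at both 12 and 36 months. Either rank analysis of covariance (Quade) or a proportional-odds model with treatment arm and the baseline answer to the same question would do; name one in advance. Keep the plain Mann-Whitney test as a sensitivity analysis.

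State how a missing baseline questionnaire is handled without using the arm, for example by a missing indicator or by imputation blind to arm, so that these patients are not dropped. Make the time points in section 11.1.1 agree with section 13.2.1, and bring the wording into line with the updated analysis plan cited in the main efficacy heading.

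The cost is a wording change, slightly more analysis work and the rule for missing baseline answers. No new data and no more patients are needed.
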